**Screening**					
Depression	CES-D	X	–	–	–
Suicidal ideation	BDI-II (Item 9)	X	–	–	–
Demographic data	–	X	–	–	–
Self-reported history of psychosis/dissociative symptoms	–	X	–	–	–
**Primary outcome**					
Depression	CES-D	X	X	X	–
**Secondary outcomes**					
*Mental health*					
Perceived stress	PSS-10	X	X	X	–
Anxiety	STAI-6	X	X	X	–
Worrying	AWQ	X	X	X	–
Emotional exhaustion	MBI-S	X	X	X	–
Behavioral activation, rumination	BADS	X	X	X	–
*Academic outcomes*					
Work impairment, productivity	PSS	X	X	X	–
College self-efficacy	CSEI	X	X	X	X
*Risk and protective factors*					
Emotion regulation skills	SEK-27	X	X	X	X
Resilience	CD-RISC	X	X	X	–
Self-compassion	SCS	X	X	X	–
Locus of control	IE-4	X	–	–	X
Self-esteem	RSES	X	X	X	–
Beliefs about stress	BASS	X	X	X	X
*Health economic measures*					
Indirect costs	TiC-P	X	X	X	–
*Health literacy and help-seeking behavior*					
Help-seeking intentions	GHSQ	X	–	–	–
Internet therapy experience	–	X	–	–	–
E-Health literacy	eHEALS	X	–	–	–
Reasons for participation	–	X	–	–	–
**Additional measures**					
Client satisfaction	CSQ-8	–	X	–	–
Intervention credibility and expectations	CEQ	X	–	–	–
Sociodemographic characteristics	–	X	–	–	X
Personality traits	BFI-10	X	–	–	X

*Mental health*. Further outcomes on mental health include perceived stress as measured by the Perceived Stress Scale 10-item version [PSS-10 (77); 10 items, range 0–40], state anxiety [short form of the Spielberger State-Trait Anxiety Inventory, STAI-6 (78, 79); 6 items, range 6–24; *at the moment*], behavioral activation, rumination and functional impairment as measured by the Behavioral Activation for Depression Scale [BADS (80); 25 items; range 0–150], and worrying [Academic Worrying Questionnaire; AWQ (81); 10 items; range 0–40]. Emotional exhaustion will be assessed using the emotional exhaustion subscale of the Maslach Burnout Inventory student version [MBI-S (82); five items, range 5–30].

*Academic outcomes*. To evaluate presenteeism and loss of productivity, the Presenteeism Scale for Students’ [PSS (83)] subscale for work impairment (Work Impairment Scale; WIS; 10 items; range 10–50) will be administered. The WIS is based on the Stanford Presenteeism Scale [SPS-6 (84, 85)] and allows to assess work-related outcomes in non-occupational samples (86, 87). Productivity losses will be assessed by an adaption of the PSS’ work output scale (WOS) investigating the percentage to which participants are able to reach their usual academic productivity. Productivity will be rated on a visual analog scale ranging from 0% = *completely unproductive* to 100% = *full productivity*. College self-efficacy will be assessed by the College Self-Efficacy Inventory [CSEI (88); 13 items; range 13–65].

*Modifiable risk and protective factors*. Risk and protective factors for mental illness include resilience as measured by the Connor-Davidson Resilience Scale short form [CD-RISC (89); 2 items; range 0–8], emotion regulation competencies [German version of the Assessment of Emotion Regulation Skills; SEK-27; State Version (90); 27 items; range 27–108], self-compassion [Self-Compassion Scale; SCS-D (91); 12 items; range 12–60], self-esteem as measured by the Rosenberg Self-Esteem Scale [RSES (92); 10 items; range 10–40], and locus of control as measured by the Short Scale for the Assessment of Locus of Control [IE-4 (93)]. The IE-4 consists of two subscales for internal and external locus of control, each consisting of two items (range 2–10). Personal beliefs about the controllability and the harmful and positive nature of stress will be assessed using the Beliefs about Stress Scales’ [BASS (94)] subscales for positive (four items; range 4–16), negative (eight items; range 8–32), and controllability beliefs (three items; range 3–12).

*Health economic measures*. Indirect costs due to presenteeism and absenteeism will be assessed using the productivity loss subscale of the Trimbos/iMTA questionnaire for costs associated with psychiatric illness [TiC-P (95)], which was adapted to the context of distant-learning students in tertiary education. With this questionnaire, participants register approximations of their working hours at university, household work, and monthly salaries when holding a job besides their studies. Indirect costs, such as the number of “work loss” days (absenteeism from work) or the number of “work cut-back” days (reduced productivity at work), can be assessed.

*Health literacy and help-seeking intentions*. To assess the help-seeking preferences of participants, the General Help-Seeking Questionnaire for personal–emotional problems [GHSQ-Per-Emot (96); seven items; range 7–77] will be administered at baseline. E-Health literacy will be assessed at baseline using the German E-Health Literacy Scale [eHEALS (97); eight items; range 8–40]. Online counseling experiences and awareness will be assessed by two items extracted from the SOEP-IS module “Internet-based psychotherapy” (98) (“have you ever utilized psychosocial or psychotherapeutic online counselling before?”; “have you ever heard of or read about Internet(-based) psychotherapies?”; yes/no). A self-constructed questionnaire will be used to assess the reasons for participating in the intervention, following the help-seeking behavior model by Rickwood, Thomas & Bradford (99).

*Additional measures*. Additional questionnaires will assess demographic variables and client satisfaction with the intervention [German version of the Client Satisfaction Questionnaire, adapted to the online context; CSQ-8; (100, 101); eight items]. Personality traits will be assessed at baseline using the 10-item Big Five Inventory [BFI-10 (102); 10 items; range 2–10 per dimension]. Treatment credibility and expectancies will be measured at baseline by administering the Credibility and Expectancy Questionnaire [CEQ (103); six items]; results for each subscale incorporated in this questionnaire will be transformed into a 100-point overall score for each participant. Participants in the IG will have the opportunity to suggest intervention improvements after every session and give feedback on each modules’ usefulness (0 = *not useful at all*, 4 = *very useful*), complexity (0 = *very complex*, 4 = *very easy*), and duration until termination (0 = *less than ½ hour*, 4 = *more than 1½ hours*) on a five-point Likert scale.

*Moderator variables*. Following variables mentioned above will be analyzed in explorative analysis of putative moderators: i) emotion regulation skills as measured by the SEK-27, ii) personality traits as assessed by the BFI-10, iii) locus of control as measured by the IE-4, iv) academic self-efficacy (CSEI), v) beliefs about stress (BASS), and vi) demographic variables. These variables were selected based on a hypothesis-generating approach, using a broad variety of possible moderators at baseline in order to detect putative moderators for sufficiently powered future studies (104).

### Statistical Analyses

*Clinical evaluation*. Analyses based on the ITT principle will be conducted, with missing data imputed using a Markov chain Monte Carlo multivariate imputation algorithm with 100 estimations per missing.

The hypothesized superiority of the Internet-based stress intervention will be tested with regard to i) change in participants’ scores of depression and secondary outcomes from baseline (T0) to post-intervention (T1) and 3-month follow-up (T2), ii) the amount of participants with treatment response, iii) the amount of participants who experienced symptom deterioration throughout the trial, and iv) the number of individuals who achieved clinically relevant amelioration of symptoms in the IG compared to the CG.

Differences in the change of symptoms between study arms will be assessed using univariate analysis of covariance with scores at baseline used as covariate. Changes in within-group scores between baseline, T2, and T3 will be explored. Effect sizes (Cohen’s *d*) will be calculated based on the imputed data set for between- and within-group changes with 95% CIs (105). To mitigate the risk of type I error inflation due to multiple testing, *p*-values will be adjusted using Holm’s method (106).

To ascertain the number of participants attaining a reliable improvement in depressive symptomatology, participants will be coded as responders or non-responders according to the widely used *Reliable Change Index* [RCI (107, 108)]. To assess the clinically relevant impact on depression for the IG compared to control, we will calculate and compare the number of participants who achieved a reduction of >50% in depressive symptoms compared to baseline at both T1 and T2.

Negative effects of the intervention will be evaluated by the number of participants with reliable deterioration concerning depression scores through the RCI.

*Moderators of treatment effects*. To assess the effect of putative moderators on changes in outcomes (i.e., T0 – T1), an ordinary least squares (OLS) regression-based framework for estimating interactions in moderation models will be used, along with simple slopes for probing interactions. In order to test the robustness of our findings and to examine differences between imputed data and complete cases, separate sensitivity analyses (109, 110) will be conducted. Moreover, to assess relevant subgroup effects, follow-up simple slope analyses for possible significant interaction effects will be conducted. The slope and significance of the intervention main effect will be evaluated for conditional values (one standard deviation below and one standard deviation above the mean) of the moderator (111). For more precise information on conditional effects of the moderators, the Johnson–Neyman technique will be applied (112).

*Cost–benefit evaluation*. According with common practice, a probabilistic approach will be used to make health-economic inferences (113). The total benefit of the intervention will be derived by subtracting productivity loss costs assessed by the TiC-P of the CG from the ones of the IG. The cost–benefit relationship will be reported by calculating the three most frequently used metrics: i) the net benefits (NB), the net monetary gain of the intervention; ii) the benefit–cost ratio (BCR), the money saved for one monetary unit invested; and iii) the return-on-investment (ROI), indicating the percentage of profit with every monetary unit invested. Bootstrapped 0.95% CIs with 2,500 replications will be estimated around these metrics.

Sensitivity analyses will be conducted to assess the robustness of the findings and to account for uncertainty regarding the actual prize of implementing the intervention into health care. Further health economic analyses will be conducted if feasible.

*Help-seeking behavior analysis*. To make assertions on the help-seeking intentions and behaviors of participants, baseline data of all participants from the GHSQ-Per-Emot (96), eHEALS (97), “awareness of online counseling,” and “reasons for participation” questionnaires will be analyzed using descriptive statistics.

*Process evaluation*. Descriptive statistics will be used for process evaluation. To assess overall user satisfaction across various domains, CSQ-8 item data will be examined. Acceptance of intervention modules will be analyzed using the module feedback of the IG. Adherence will be assessed by analyzing intervention completion rates tracked within the intervention platform.

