### Assessment of Eligibility and Randomization

Individuals who declare their interest in participating in the study will receive an online letter with detailed information about the study procedure and will be asked to provide an e-mail address as well as a first and last name (which may be pseudonyms) for their intervention platform profile. Applicants will be informed that withdrawal from the study is possible at any time without negative consequences and that all collected case data can be deleted on request during the study. Participants will then be asked to fill out the online screening questionnaire.

Individuals fulfilling all inclusion and none of the exclusion criteria will be asked to fill out an informed consent form. Individuals who provide us with their informed consent will be invited to fill out the baseline assessment, which will take approximately 30 min to complete. Subsequently, individuals will be randomly allocated to either the IG or the CG. Randomization will take place at a ratio of 1:1 and a block size of 2 using an automated computer-based random integer generator (*Randlist*, Datinf GmbH, Tübingen, Germany) and will be performed by a researcher who is not involved in the study. Participants will not be blinded to study conditions, yet during the randomization process, the allocation will be concealed from participants, researchers involved in recruitment, and e-coaches.

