### Sample Size

We aim to include *N* = 200 participants, allowing for a between-trial arm group comparison against a statistically relevant effect size threshold of *d* = 0.40, a power (1 − β) of 80%, and an alpha of 0.05 (two-tailed) for the intention-to-treat (ITT) analysis (54). A recent meta-analytic review for Internet-based stress interventions reported effect sizes of *d* = 0.64 for perceived stress in guided interventions but considerably smaller effect sizes for unguided programs (*d* = 0.34 for depression, *d* = 0.32 for anxiety) (27). Results for Internet-based interventions addressing psychological distress in tertiary education are mixed, ranging from non-significant findings to moderate-sized effects in favor of the respective intervention (55–59). Thus, we aim for an effect size of *d* = 0.40.

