### Primary Outcome

The primary outcome is symptoms of depression as measured by the German version of the CES-D 20-item version [ADS (51); 20 items; range 0–60] at post-treatment (T1). Participants will be asked to indicate the frequency of depression-specific symptoms for a retrospective timeframe of 2 weeks on a four-point Likert scale [0 = *rarely or none of the time present* (less than 1 day), 3 = *most of the time present* (5–14 days); e.g., “During the past two weeks I had trouble keeping my mind on what I was doing.”]. Higher scores indicate greater depression severity. The CES-D shows high correlations up to *r* = 0.90 with other measures such as the Hamilton Depression Scale or the Beck Depression Inventory, and has a high retest reliability of *r*
*_tt_* = 0.81, indicating the high internal validity of this instrument (51).

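### The Holm adjustment has no defined family and does not exempt the single primary test, while the 80% power is stated for one comparison at unadjusted two-sided 0.05

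*Protocol article*

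**What the plan says.** - **Primary outcome.** "The primary outcome is symptoms of depression as measured by the German version of the CES-D 20-item version", at post-treatment (T1). The Abstract says the same: one scale, one time point.
- **Sample Size.** N = 200 "participants, allowing for a between-trial arm group comparison" at d = 0.40, 80% power and "an alpha of 0.05 (two-tailed) for the intention-to-treat (ITT) analysis". No multiplicity allowance enters this calculation.
- **Statistical Analyses, Clinical evaluation.** Superiority is to be tested on "scores of depression and secondary outcomes from baseline (T0) to post-intervention (T1) and 3-month follow-up (T2"), and also on treatment response, deterioration and clinically relevant improvement. Between-arm differences are assessed by ANCOVA with the baseline score as covariate. The same paragraph ends with the multiplicity rule: "To mitigate the risk of type I error inflation due to multiple testing", p-values are to be Holm-adjusted. The Clinical evaluation text does not single out the primary outcome, sets no testing order and does not define the family.

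**The concern.** A single pre-specified primary test needs no multiplicity correction. If it is placed in a Holm family with the secondary scales, two things follow. It faces a threshold stricter than the 0.05 the trial was sized for. Its significance also depends on how many secondary outcomes are analysed and how they turn out.

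The planned effect lies where this matters. With 100 per arm, an observed d of exactly 0.40 gives p of about 0.005. That is clearly significant at 0.05, but it can fail after a Holm adjustment over a family of realistic size. A trial that finds what it was designed to find could be called positive or negative depending on a choice the text leaves open. Left open, that choice could also be made after the p-values are known.

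**Working it through.** **Inputs from the article.** N = 200, d = 0.40, 80% power, two-sided alpha 0.05 (Sample Size); "Randomization will take place at a ratio of 1:1" (Assessment of Eligibility and Randomization), so 100 per arm; ANCOVA on the baseline score (Statistical Analyses).

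**1. Reproduce the plan's figure.** n per arm = 2(z₀.₉₇₅ + z₀.₈₀)²/d² = 2(1.960 + 0.842)²/0.40² = 98.1, so 99 per arm and 198 in total. With 100 per arm, power is 80.7% (normal approximation) or 80.4% (noncentral t). N = 200 is right on its inputs and has almost no margin.

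**2. Family size m (assumption; the article does not state it).** Scores measured at T1, from Table 3 and the outcome descriptions: CES-D (1); PSS-10, STAI-6, AWQ, MBI-S, BADS (5); work impairment, productivity, CSEI (3); SEK-27, CD-RISC, SCS, RSES (4); three BASS subscales (3). The sum is 16, or 32 over T1 and T2. The smallest case is m = 2, for example CES-D at T1 and T2 only.

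**3. Holm's first step.** The smallest p-value is compared with 0.05/m. The expected z-statistic for the primary is 0.40 × √(100/2) = 2.83, so power ≈ Φ(2.83 − z₁₋₀.₀₂₅/ₘ).

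| m | 0.05/m | critical z | power, normal | power, t | total N for 80% |
|---|---|---|---|---|---|
| 1 | 0.0500 | 1.960 | 80.7% | 80.4% | 198 |
| 2 | 0.0250 | 2.241 | 72.1% | 71.5% | 238 |
| 16 | 0.0031 | 2.955 | 45.0% | 43.7% | 362 |
| 32 | 0.0016 | 3.163 | 36.9% | 35.6% | 402 |

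**4. Full step-down procedure.** Holm relaxes the threshold as other tests are rejected, so step 3 is a lower bound. In simulations with correlation 0.5 between tests and secondary d from 0.1 to 0.4 (both assumed), power for the primary is about 72–78% (m = 2), 44–56% (m = 16) and 37–46% (m = 32). The lower end applies when secondary effects are small, the upper end when they equal the primary effect. Correlations of 0 or 0.7 move these figures by only a few points, and none of these scenarios reaches 80%.

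**5. An observed d of 0.40.** z = 2.83, p ≈ 0.0047. Holm rejects only if p ≤ 0.05/(m − k), where k is the number of tests with smaller, already rejected p-values. Since 0.05/0.0047 ≈ 10.7, m − k must be 10 or fewer. So at least 6 of the 15 other tests (m = 16), or 22 of 31 (m = 32), must be rejected ahead of it.

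**6. Gain from ANCOVA.** If d = 0.40 is on the raw-SD scale, a baseline–outcome correlation r reduces the residual SD to √(1 − r²). At r = 0.5 (assumed), first-step power is 90.4% for m = 1, 84.7% for m = 2, 62.2% for m = 16 and 54.1% for m = 32. To regain 80% at the first step, r must be about 0.40 (m = 2), 0.67 (m = 16) or 0.71 (m = 32).

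**The case against.** The strongest reply is that the article can be read consistently. The Holm sentence states its purpose, which is inflation from multiple testing. A single primary at a single time point creates none, and the Sample Size section assigns 0.05 to the comparison it powers. On that reading Holm covers only the remaining tests, and 80% power stands. Defining a family is also often left to an analysis plan, which is not shown here. And even the literal reading errs towards caution: Holm controls familywise error, so no false-positive claim arises from it.

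Much of this stands. The text does not say that all p-values are adjusted. A reader might infer that the primary is certainly in the family, but the documents do not settle it. A reader might also add the three responder-type endpoints at two times and count 38 tests. That is poorly supported, because the Holm sentence closes the ANCOVA paragraph, before the responder and deterioration rules appear.

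ANCOVA could offset the loss: fully in a family of two with r of about 0.40, and in larger families with r near 0.7. The only correlation the article gives is a CES-D retest reliability of 0.81. That is not a seven-week correlation in a sample selected at CES-D ≥ 16, so it neither secures the gain nor rules it out.

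What does not stand is that this is merely omitted detail. The article itself states both the alpha and an unqualified adjustment rule, and followed literally the two do not match.

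**Conclusion.** The point holds as a mismatch between a stated power and an unqualified adjustment rule, at moderate severity. The sample-size arithmetic is correct. It does not follow that the trial is underpowered for its primary question. That would require the primary to be in the Holm family, which the text neither states nor excludes.

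If it is in the family, the 80% is not delivered on the sample-size inputs. The shortfall runs from a few points with 2 tests to roughly half the stated power with 32. These figures rest on the assumed family sizes, the between-test correlation and the secondary effects, and they take no credit for ANCOVA. If it is not in the family, power is as stated and only the wording is deficient. Both readings need the same clarification.

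**What to change.** Add to Statistical Analyses, before outcome data are analysed: *CES-D at T1 (ANCOVA, intention-to-treat) is tested once at two-sided 0.05 without adjustment and alone decides the primary hypothesis. Holm's method is applied to the remaining tests: secondary scores at T1, all outcomes at T2, RCI response, reduction of more than 50%, and reliable deterioration.*

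The cost is this short addition. It needs no extra participants, loses no error control on the primary claim, and brings the analysis into line with the stated 80% power.

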This trial will employ a cutoff for elevated symptoms of depression, although not restricting eligibility to individuals showing symptoms of full-blown depression only. Although in its content, the intervention at hand focuses on academic stress, we did not decide for a cutoff for perceived stress, as this trial is aimed at evaluating the intervention’s effectiveness as an intervention instrument in individuals with an indicated risk for depression and in individuals potentially suffering from major depression. Perceived stress has been associated with the development (33) and worse trajectories (34, 35) of clinical depression. The potential of Internet-based stress interventions as an early intervention and treatment instrument in depressive target groups, however, has not yet been evaluated. Mental health stigma, a known barrier to treatment utilization, has been shown to be greatest among highly distressed individuals with low depression literacy (116). If the intervention evaluated in this trial is found to be effective, Internet-based stress interventions could be investigated as a potential mean to address depression in individuals for whom a conventional mental health disorder treatment would not be an option.

We will compare the effects of the intervention to an Internet-based psychoeducation program of similar length. Meta-analytic evidence suggests that Internet-based interventions for college students show moderate to large effect sizes when compared to a waiting CG. This superiority, however, could not be ascertained when compared to active CGs (117). Treatment expectancies have been discussed as an artifact in clinical evaluation studies utilizing waitlist CGs. Participants waiting for treatment may be less motivated to initiate health-related behavior changes (118–120), which could over-accentuate effects attributed to an intervention (120, 121). Findings in this trial will provide the opportunity to investigate the effects of an Internet-based intervention employing evidence-based cognitive–behavioral techniques compared to a CG in which participants are also actively engaged.

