Findings of this trial will have some limitations. First, an open recruitment strategy is employed, in which potential participants are actively recruited from the student population. Therefore, we cannot rule out selection bias, with more motivated individuals attaining access to the study. Second, due to feasibility reasons, this trial is somewhat underpowered to reliably detect significant treatment moderators. This might impede finding statistically significant factors contributing to this interventions’ effectiveness that would have been detected in a larger study sample (122, 123). Same applies to health-economic inferences, for which a probabilistic approach will be applied in this study. Third, due to logistic reasons, this trial will only use self-administered questionnaires and will not assess diagnostic status or physiological measures.

There is a growing number of studies investigating the efficacy of Internet-based interventions in reducing various symptoms of mental illness (124, 125). Much less is known, however, on the potential of such interventions in distance-learning student samples, and their impact on academic functioning, for which this study will provide tangible empirical results. Results will also provide the opportunity to investigate the practicability of Internet-based stress interventions as an approach to address mental health issues in individuals with subthreshold or full-blown symptoms of depression and increase their use of health services.

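### The moderator models state no baseline covariate, unlike the main ANCOVA, and baseline CES-D is not among the listed moderators; both can be put right with data already collected

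*Protocol article*

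**What the plan says.** Protocol article, Statistical Analyses:

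- **Clinical evaluation.** Differences between arms in symptom change are to be tested by "univariate analysis of covariance with scores at baseline used as covariate".
- **Moderators of treatment effects.** The target is the "effect of putative moderators on changes in outcomes" between T0 and T1, in an ordinary least squares framework with interaction terms, simple slopes one standard deviation either side of the moderator mean, and the Johnson–Neyman technique. No covariate is named, either as included or as left out.

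The moderators are itemised under Secondary Outcomes, in the paragraph that begins "Following variables mentioned above will be analyzed in explorative analysis of putative moderators". They are SEK-27, BFI-10, IE-4, CSEI, BASS and demographic variables. CES-D is not listed, and Table 3 gives it a dash in the putative-moderator column.

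Three other places bear on this. The Background makes the study of moderators one of four goals. Participants sets entry at CES-D ≥ 16 with no upper limit. The Discussion says the intervention is to be evaluated "in individuals with an indicated risk for depression and in individuals potentially suffering from major depression", and later concedes that "this trial is somewhat underpowered to reliably detect significant treatment moderators".

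**The concern.** There are two separate points.

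The first is the model. The baseline covariate is named for the main comparison and not for the moderator models two paragraphs later. An analyst who follows the moderator paragraph to the letter would regress raw change on arm, moderator and their product. That discards information from a score every participant supplies at T0, in the analyses where the authors already say power is short.

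The second is the list. Symptom severity at entry defines eligibility and varies from subthreshold to full-blown, yet it is not one of the prespecified modifiers. Any later look at whether the effect differs by severity would then be post hoc. An interaction found for a listed variable that correlates with severity, as emotion regulation skills or self-efficacy may, could not be set beside a planned severity result.

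**Working it through.** **1. The plan's own figure.** The Sample Size section gives "We aim to include *N* = 200 participants", d = 0.40, and "a power (1 − β) of 80%, and an alpha of 0.05 (two-tailed"). By the normal approximation, n per arm = 2(1.960 + 0.842)² / 0.40² = 98.1, so 99 per arm and 198 in total. At 100 per arm, power is 0.807 (0.804 by the t-test). The stated N = 200 reproduces. It concerns the main comparison; the article gives no figure for the moderator analyses.

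**2. Residual variance.** Let r be the correlation of T0 and T1 scores and k = SD(T0)/SD(T1). In units of the T1 variance:

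- change without the baseline score: 1 + k² − 2rk
- change or T1 with the baseline score: 1 − r²
- ratio, adjusted to unadjusted: (1 − r²)/(1 + k² − 2rk)

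The first variance minus the second is (k − r)², which cannot be negative. Adjustment therefore never raises residual variance, apart from one degree of freedom.

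**3. Numbers.** Neither r nor k is in the article; both are assumed. The CES-D retest reliability of 0.81 is not the T0–T1 correlation in this trial. I take r = 0.4 to 0.6. For k I take 1 (equal spread) and, as an illustration, 0.75, because entry only at CES-D ≥ 16 may narrow the T0 spread while T1 scores are free to spread out. The interaction is per standard deviation of the moderator, with SE = 2·√(variance/200). Power is for an assumed interaction of 0.30 T1 standard deviations, two-sided alpha 0.05.

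| k | r | Unadjusted variance | Adjusted variance | Ratio | Fall in SE | Equivalent sample gain | Power, unadjusted → adjusted |
|---|---|---|---|---|---|---|---|
| 1 | 0.4 | 1.20 | 0.84 | 0.70 | 16% | 43% | 49% → 64% |
| 1 | 0.5 | 1.00 | 0.75 | 0.75 | 13% | 33% | 56% → 69% |
| 1 | 0.6 | 0.80 | 0.64 | 0.80 | 11% | 25% | 66% → 76% |
| 0.75 | 0.4 | 0.9625 | 0.84 | 0.87 | 7% | 15% | 58% → 64% |
| 0.75 | 0.5 | 0.8125 | 0.75 | 0.92 | 4% | 8% | 65% → 69% |
| 0.75 | 0.6 | 0.6625 | 0.64 | 0.97 | 2% | 4% | 74% → 76% |

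**4. Validity.** Simulation with N = 200, k = 1, r = 0.3, 0.5 and 0.7, moderator–baseline correlation 0 or 0.4, and 3,000 runs per setting: the unadjusted interaction estimate is unbiased and its type I error lies between 0.047 and 0.058. The cost is precision only.

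**5. Change or T1.** Once the baseline score is a covariate, subtracting it from the outcome alters only its own coefficient (by 1 in absolute value). The interaction estimate and its standard error are the same up to sign.

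**6. Severity as a hidden modifier.** Take a true severity interaction of 0.30 and a moderator that correlates 0.4 with severity but has no interaction of its own. The expected spurious interaction is 0.30 × 0.4 = 0.12. The simulation (r = 0.5) gave 0.120 without and 0.118 with the baseline main effect. Adjusting for baseline does not remove this; only an arm × CES-D term speaks to it. These inputs are illustrative.

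**The case against.** The strongest reply is that leaving out the baseline score is inferred from silence. The moderator paragraph lists no covariates at all, the main analysis uses the word change for a baseline-adjusted model, and a journal article commonly leaves covariate lists to a fuller document that is not shown here. This stands. The article cannot be said to exclude the baseline score; it can only be said that it states the covariate in one place and not in the other, so that a literal reading gives an unadjusted model.

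A reader might infer that regression to the mean, in a sample selected on high CES-D, distorts the moderator results. It does not under randomisation: it is expected equally in both arms, and the simulation shows no bias and nominal type I error.

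A reader might also take sample gains of 25–43% as the size of the loss. They require equal T0 and T1 standard deviations. With k = 0.75 they shrink to about 4–15%.

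On the list, it can fairly be said that the choice of exploratory moderators belongs to the investigators, and that the Discussion describes who is studied without posing a question about effect modification by severity. That also stands: no passage states such a hypothesis, so the trial is not failing to answer a question it set itself. Nor does the omission make severity impossible to examine, since CES-D is measured at T0. What remains is that a modifier to which the trial's own rationale points is not prespecified, although moderators are a stated goal and the list is meant to be broad.

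**Conclusion.** The point holds as a matter of precision and prespecification, not of validity. If the moderator models are fitted as literally written, residual variance is larger than it need be: adjustment would save about 3–30% over r = 0.4–0.6 and k = 0.75–1, and the saving cannot be negative. The range rests on assumed r and k, and the loss arises only if the baseline score is in fact left out. The absence of baseline CES-D from the moderator list is documented in two places and needs no assumption. The moderator analyses are exploratory and admitted to be underpowered, and the primary result is untouched, so this is a modest improvement rather than a fault in the trial's main conclusion.

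**What to change.** 1. In the moderator paragraph of Statistical Analyses, state that each model contains the baseline score of its outcome: arm + baseline score + moderator + arm × moderator. Either change or the T1 score may then be the outcome.
2. Add continuous baseline CES-D to the moderator list and mark it in Table 3, as one exploratory moderator with the planned simple-slope and Johnson–Neyman output. When CES-D is also the outcome, the baseline and moderator terms are the same variable and enter once.
3. Optional: for moderators that correlate with severity, repeat the model with an arm × CES-D term. The correlated term will tend to widen the interval, so this belongs with the sensitivity analyses.

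No new data are needed. The cost is a sentence of wording and one more exploratory test in an already underpowered set. Fixing it before analysis keeps the severity result prespecified.
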